## Abstract

**Background:**

Improving the functional recovery of patients with DoC remains one of the greatest challenges of the field. Different theories exist about the role of the anterior (prefrontal areas) versus posterior (parietal areas) parts of the brain as hotspots for the recovery of consciousness. Repetitive transcranial magnetic stimulation (rTMS) is a powerful non-invasive brain stimulation technique for the treatment of DoC. However, a direct comparison of the effect of TMS treatment on the front versus the back of the brain has yet to be performed. In this study, we aim to assess the short- and long-term effects of frontal and parietal rTMS on DoC recovery and characterize responders phenotypically.

**Methods/design:**

Ninety patients with subacute and prolonged DoC will be included in a two-part multicenter prospective study. In the first phase (randomized controlled trial, RCT), patients will undergo four rTMS sessions in a crossover design over 10 days, targeting (i) the left dorsolateral prefrontal cortex (DLPFC) and (ii) the left angular gyrus (AG), as well as (iii & iv) their sham alternatives. In the second phase (longitudinal personalized trial), patients will receive personalized stimulations for 20 working days targeting the brain area that showed the best results in the RCT and will be randomly assigned to either active or sham intervention. The effects of rTMS on neurobehavioral and neurophysiological functioning in patients with DoC will be evaluated using clinical biomarkers of responsiveness (i.e., the Coma Recovery Scale-Revised; CRS-R), and electrophysiological biomarkers (e.g., power spectra, functional and effective connectivity, perturbational complexity index before and after intervention). Functional long-term outcomes will be assessed at 3 and 6 months post-intervention. Adverse events will be recorded during the treatment phase.

**Discussion:**

This study seeks to identify which brain region (front or back) is best to stimulate for the treatment of patients with DoC using rTMS, and to characterize the neural correlates of its action regarding recovery of consciousness and functional outcome. In addition, we will define the responders’ profile based on patients’ characteristics and functional impairments; and develop biomarkers of responsiveness using EEG analysis according to the clinical responsiveness to the treatment.

**Clinical Trial Registration:**

https://clinicaltrials.gov/ct2/show/NCT04401319, Clinicaltrials.gov, n° NCT04401319.

## Introduction

### Disorders of consciousness

Severe brain injury may result in disorders of consciousness (DoC) (1). Such neurological conditions range from coma (i.e., no wakefulness and reflex behaviors only), to the unresponsive wakefulness syndrome (UWS/*VS*) (i.e., recovery of wakefulness with reflex behaviors) (1), and the minimally conscious state (MCS) (i.e., reproducible and purposeful behaviors, such as visual pursuit and responses to commands) (2). Moreover, MCS can be subcategorized into MCS- and MCS+ depending on the presence or absence of language processing. MCS- patients can show visual fixation and pursuit, localization of noxious stimuli or emotionally contingent behavior, while MCS+ patients show reproducible command-following, intelligible verbalization or intentional communication (2). Patients are thought to have emerged from MCS when they display functional communication or functional use of two objects in two consecutive assessments (3).

### Therapeutic options in DoC

In the last decade, few studies have investigated treatment options for patients with DoC (4). Recently, some RCTs have been performed, focusing on pharmacological [e.g., amantadine (5), zolpidem (6)] and non-pharmacological interventions to improve patients’ neurobehavioral functioning. Regarding the latter, a recent meta-analysis studying the effect of non-invasive brain stimulation found evidence for left dorsolateral prefrontal cortex (DLPFC) transcranial direct current stimulation efficacy against sham on behavioral measures in MCS patients with low to moderate effect sizes (7).

Among neuromodulation techniques, repetitive transcranial magnetic stimulation (rTMS) is a non-invasive brain stimulation tool that can modulate cortical excitability, enhance neural plasticity, and induce strong neuromodulatory effects that outlast the period of stimulation (8, 9), especially when applied repeatedly. Thus, it is now established that TMS holds an important role in promoting and monitoring functional recovery in severe brain injury (10). In the field of DoC, some studies have investigated rTMS-induced changes on behavior (11) and electrophysiology (12) or both in patients with severe brain damage (12–17). However, these protocols usually differ in several experimental parameters (e.g., stimulation site, stimulation intensity, number of sessions delivered), making it difficult to draw any conclusion on an effective stimulation protocol at this stage.

To date, most studies have investigated the effects of high-frequency (20 Hz) primary motor cortex stimulation to elicit recovery in DoC patients, showing poor to null clinical improvement at the group level (18–20). However, one RCT comparing the effects of 20 Hz stimulation over the motor cortex and the prefrontal cortex to sham stimulation demonstrated improvement in all groups, but of highest magnitude in the motor cortex group (16).

Regarding other target locations, some RCTs recently reported significant clinical changes in patients (i.e., increased behavioral total scores after intervention) when targeting the left prefrontal regions using multiple sessions (i.e., between 10 to 30 sessions) of high-frequency (i.e., 10–20 Hz) rTMS (21–23).

Eventually, two recent open label studies exploring the effect of rTMS over the left parietal cortex found improved behavioral total scores in MCS patients (24) and even in some UWS/*VS* patients (15). Hence, from these studies, it becomes evident that rTMS is feasible in DoC patients, and that some protocols involving specific target parameters may elicit clinical as well as physiological changes (25), especially in the prefrontal and anterior parietal regions (i.e., DLPFC and angular gyrus, AG). However, to our knowledge, although these two stimulation sites seem relevant, there is currently no study comparing the effect of DLPFC versus AG rTMS in DoC patients.

### Consciousness theories to support the role of frontal and parietal rTMS as therapeutic candidates

Despite their indisputable core importance in the dynamic brain processes that are essential in consciousness circuitry, studies trying to isolate the role of frontal versus posterior cortical regions in the emergence of consciousness show contrasting evidence (26). However, it is well established that DoC are caused by widespread dysfunctions preventing the interaction between these areas (27). A common model accounting for post-comatose DoC is the fronto-parietal mesocircuit model (28, 29). This model supports the idea that deafferentation and loss of neurons due to a severe brain injury could induce a reduction of thalamo-cortical and thalamo-striatal functional connectivity from the central thalamus, and consequently, further decreases the activity of the central thalamic and the fronto-parietal networks (30). Figure 1 illustrates the mesocircuit model and the hypothetical changes induced by therapeutic rTMS. Beside this model, the integrated information theory (IIT) postulates that the response of the brain to perturbation needs to be integrated and differentiated – as indexed by the perturbational complexity index (PCI), a proxy for the degree of these components in response to an external perturbation (31). IIT suggests that the posterior part of the brain is the hotspot of consciousness as an experimental hypothesis (26, 27, 32). In contrast, the global neuronal workspace theory suggests that the hotspot of consciousness is located at the front of the brain, and that consciousness arises from ignition (33, 34). In parallel with their theoretical implications, these different models can also guide therapeutic perspectives aimed at restoring consciousness functioning. Thus, approaches acting over these critical structures could hypothetically restore the loops between the central thalamus, the cortex, the striatum and the globus pallidus interna. The loops within and between frontal and parietal cortex can be indexed by EEG-based functional connectivity (35).

**Figure 1 fig1:**
[figure not shown]
Mesocircuit model and rTMS. The deafferentation of thalamostriatal and corticostriatal outflows following widespread neuronal disruption leads to reduced activity of the striatum, resulting in an inhibition of thalamic activity and decreased thalamo-cortical connectivity and cortical activation. By stimulating the frontal or the parietal cortex, rTMS may hypothetically supply for the missing thalamic excitatory inputs through the reestablishment of cortico-subcortical connectivity. Adapted from Giacino et al. (28).

In the light of the above theories, we here propose to investigate the effects of rTMS over the frontal and the parietal areas of the brain to promote recovery of consciousness in patients with DoC. More specifically, we here propose to target the DLPFC, as it is involved in a number of higher-level behaviors and cognitive processes (36, 37) as well as the AG, that occupies a key neuroanatomical position within the parietal structures of the default mode network, a specific network that has been shown to correlate with the level of responsiveness in DoC patients (38, 39).

## Study objectives and hypotheses

Although the choice of stimulation site is becoming an increasingly important issue in the neurostimulation community, no clinical RCT has been performed to determine which stimulation site might be associated with the best clinical outcomes after severe brain injury. Hence, this is the study’s main objective. In a second phase, we will provide a patient-tailored individualized therapy approach through a personalized medicine design. We aim to (1) improve the functional recovery of patients with DoC using either frontal or parietal rTMS, (2) investigate the neurophysiological effects of rTMS interventions in these two distinct brain areas using resting state electroencephalography (EEG) and TMS-EEG, (3) determine the phenotype of clinical responders (i.e., that is, any patient who displayed new sign(s) of consciousness following stimulation that was never displayed during the screening phase nor at baseline), and (4) assess the long-term efficacy of the rTMS interventions in terms of functional outcomes through follow-up assessments.

Our primary hypothesis for the RCT crossover is that a significant portion of our patient sample will show increased responsiveness (i.e., overall CRS-R scores and signs of consciousness) following a single session of DLPFC or AG rTMS (responders). We also expect some patients to show stronger EEG connectivity at the whole brain level, especially in frontoparietal regions (20) compared to sham stimulation.

As for the second phase of the study, as a primary outcome, we hypothesize that patients stimulated over the left DLPFC or the left AG for 20 consecutive sessions will show higher levels of behavioral improvement compared to patients in the sham stimulation group.

Moreover, as secondary hypotheses, we expect that these changes in responsiveness will be associated with modifications in brain complexity and functional connectivity. We postulate that the EEG resting state metrics (e.g., spectral power metrics, connectivity) in the frequencies of interest (i.e., delta, theta and alpha bands) and the TMS-EEG derived measures of brain responses (e.g., PCI) will be modulated by the rTMS intervention and associated with behavioral responses to therapy.

As exploratory hypotheses, we also expect that MCS patients will be more likely to respond to the treatment than patients in UWS/VS. We also expect patients who received the active treatment to obtain better outcome at 3 and 6 months following the end of the intervention period compared to the sham group. No adverse event is expected in any of the three study arms.

## Methods

### Design

This multicenter study consists of two parts: a within-subject, four-arm crossover double-blind RCT and a three-arm parallel double-blind personalized & randomized controlled trial. Both parts will be conducted at the neurological rehabilitation centers William Lennox (Ottignies-Louvain-la-Neuve Belgium), Therapiezentrum Burgau (Burgau, Germany), and Schön Klinik Bad Aibling-Harthausen (Bad Aibling, Germany). A pilot has already been conducted to assess our methods and the protocol as well as our ethical committee have been adapted based on that early testing phase. Therefore, the trial will be preceded by a new pilot phase on a minimum of two patients with the current study design to re-assess feasibility as well as tolerability of our protocol.

### Population and recruitment

Ninety patients with DoC after severe brain injury will be included in the study. Written informed consent will be obtained from patients’ legal surrogates and the patients themselves if they recover functional communication. The study will be conducted in accordance with the Declaration of Helsinki in its latest form. The study protocol was approved by the University Hospital of Liege Ethics Committee under the reference number 2019/277 (BE021921888) and the Ethics Committee of the Medical Faculty at Ludwig-Maximilians-University Munich under the reference number 20–0873 (Therapiezentrum Burgau and Schön Klinik Bad Aibling-Harthausen) and registered on Clinicaltrials.gov (identifier NCT04401319).

Eligibility will be derived from medical records and clinical visits. Inclusion criteria will be the following: patients with DoC due to acquired brain injury classified according to international guidelines as UWS/*VS* or MCS with at least two repeated behavioral assessments with the CRS-R within 10 days prior to inclusion; ≥ 18 years old; > 28 days post-injury; and stable vital parameters. As for exclusion criteria, they will be the following: no previous neurological deficits prior to the brain lesions; no pregnancy; no contraindication for TMS (e.g., uncontrolled epilepsy, that is, seizure within 4 weeks prior to enrollment, metallic implant in the skull, pacemaker, craniotomy under the stimulated site, peri-ventricular shunting device, sensitive skin); no sedative drugs or drugs thought to interfere with brain stimulation such as Na or Ca channel blockers (e.g., carbamazepine) or NMDA receptor antagonists (e.g., dextromethorphan); no drugs or substances which have strong potential of seizure induction (imipramine, amitriptyline, doxepine, nortriptyline, maprotiline, chlorpromazine, clozapine, foscarnet, ganciclovir, ritonavir, phencyclidine, ketamine, gamma-hydroxybutyrate, alcohol, and theophylline); and no current enrollment in other therapeutic clinical trial for the whole duration of the treatment protocol and follow-up. Patients will still receive all the standard medical and para-medical care from their facilities such as sensory stimulation or physical therapy. Table 1 summarizes all inclusion and exclusion criteria. In the present study, we will not exclude patients with lesions at the stimulation site (i.e., over the DLPFC or the AG) as it will enable us to document if patients with this structural profile show a lower rate of clinical responders compared to patients with healthy brain tissue at the target location.

**Table 1 tab1:** Study inclusion and exclusion criteria.

Inclusion criteria	Exclusion criteria
Age ≥ 18 years old	Previous neurological deficits prior to the brain lesions
Acquired cerebral damage of known etiology	Pregnancy
Diagnosed in UWS/*VS* or MCS as defined by at least two CRS-R assessments performed during the screening period Time since injury >28 days	Contra-indication for TMS (e.g., uncontrolled epilepsy, that is, seizure within 4 weeks prior to enrollment, metallic implant in the skull, pacemaker, craniotomy under the stimulated site, implanted brain device)
Informed consent given by the legal surrogate	Sedative drugs or drugs thought to interfere with brain stimulation such as Na or Ca channel blockers or NMDA receptor antagonists Concurrent enrollment in any other therapeutic experimental trial

### Procedure

#### Screening phase & enrollment

The study procedure will start at the earliest on the 28th day post-injury. All patients will be evaluated repeatedly (i.e., at least twice within 10 days prior to inclusion) with the CRS-R to confirm DoC diagnosis before enrollment. Existing CT or MRI-scans will be used to document structural lesions for neuronavigation-based targeting within 28 days before inclusion. Following screening phase, the legal surrogate of each eligible patient will be contacted for oral and written informed consent. After inclusion, every patient will first be enrolled in the crossover RCT protocol and will thus undergo four rTMS sessions. Based on the analysis of the patient’s best behavioral or electrophysiological response to either left DLPFC or left AG stimulation, the personalized protocol (4 weeks) will be started up to a week later.

#### Randomized crossover trial

Within 10 days, all patients will undergo four rTMS sessions that will be administered in a randomized order and separated by a 72 h washout period: (i) one real stimulation over the left DLPFC, (ii) one real stimulation over the left AG, (iii) one sham stimulation over the left DLPFC, and (iv) one sham stimulation over the left AG. In this study, we chose to stimulate the left hemisphere because it tends to be more often targeted in non-invasive brain stimulation trials with DoC patients than the right hemisphere and because it was shown to have more promising results in other top-down electromagnetic-based techniques such as transcranial direct current stimulation (40). Randomization of the sequence of the four stimulation sessions will be stratified for gender, etiology, time post-injury, and diagnosis using computerized random number generator. Standardized behavioral assessments will be performed by experienced clinicians who will be blind to the nature of the sessions. The CRS-R will be performed before and after each stimulation session. Fifteen minutes of resting state high-density EEG will be performed directly before and after the stimulation (i.e., after the behavioral evaluation pre-stimulation and before the behavioral evaluation post-stimulation). Together with the EEG, electrooculogram (EOG) and electrocardiogram (ECG) will be recorded. See Figure 2 for the randomized crossover trial protocol.

**Figure 2 fig2:**
[figure not shown]
rTMS crossover RCT protocol. Patients’ state of consciousness will be repeatedly assessed with the CRS-R to confirm DoC diagnosis and existing MRI or CT images will be collected. All patients included will then receive 4 sessions (frontal rTMS; parietal rTMS; frontal sham: parietal sham) of 20 min 20 Hz rTMS administered in a double-blind and randomized order within 10 days and separated by a 72 h washout period. Each session will be directly preceded and followed by CRS-R assessments and 15 min resting state EEG recordings. Patients will then be allocated to one of the groups of Study 2.

#### Personalized parallel trial

This trial will include three arms (i.e., DLPFC rTMS, AG rTMS and the sham-controlled condition). After a 1 week washout period following the randomized crossover study, the personalized parallel trial will be conducted. Based on their behavioral (primary) or electrophysiological (secondary) responses to either the left DLPFC or left AG treatment in the crossover RCT, patients will be assigned to one of two groups (i.e., DLPFC group if the patient was a responder to the DLPFC stimulation; AG group if the patient was a responder to the AG stimulation). If no behavioral response nor EEG change from the RCT could be obtained regarding the best stimulation hotspot or if the patient is a responder to both sites, the patient will be randomized into one of the two stimulation hotspots in a 1:1 ratio. Then, all patients will be randomized between the experimental condition and the sham condition following a 2:1 ratio by a randomized order generator. Only the investigator in charge of the randomization will be aware of the patients’ group allocation. The assigned intervention (i.e., active stimulation versus sham stimulation) will be concealed from the patient, the family, the care providers and all investigators involved in the patient’s assessment for the whole duration of the treatment phase. The evaluator will stay blind from the sequence as well as from the stimulation group during treatment and follow-up. Moreover, analyses will be conducted in a triple blind fashion (see *rTMS device* point for more information about blinding methods). All patients included in the trial will undergo 4 weeks (i.e., 20 working days) of stimulation. Behavioral effects will be assessed with the CRS-R at baseline and once a week during the 4 weeks stimulation protocol. Fifteen minutes of high-density EEG resting state will be performed right before and right after the first session as well as before and after the last session. Eventually, TMS-EEG acquisitions will be performed the first and last day of the 4 weeks protocol. As we will assess the effects following a single session (first stimulation session) and after 4 weeks of rTMS, we will be able to compare the effect of a single versus repeated sessions of stimulation. Figure 3 depicts an overview of the two studies.

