#### Secondary outcomes

In the RCT, the change in EEG metrics between post and pre stimulation of each session will be estimated and will stand as our secondary outcome. More specifically, analyses will focus on changes in whole brain connectivity markers as well as on power spectrum for each frequency band and brain response complexity. The alpha-band participation coefficient will be used to determine the response of a patient to the stimulation in the crossover stimulation protocol by means of pre and post stimulation differences. The same metrics will be computed and compared for the longitudinal trial before and after the 4 weeks treatment period. Additionally, for the latter study, TMS-EEG derived PCI will be computed and compared using the same method. TMS-EEG data will be analyzed with EEGLAB,^1^ FieldTrip,^2^ Brainstorm,^3^ MNE-Python^4^ and in-house MATLAB (SSP BioMedical Data Analysis Package; SiSyPhus Project; Version 2.5e) and Python scripts. The resting state data will be analyzed with a dedicated analysis pipeline (35). Continuous EEG resting state data will be filtered between 0.5 and 45 Hz and segmented into 10 s epochs. Then, data will be thresholded to remove clear-cut artifacts. EOG and ECG will be used to inform the removal of artifactual data epochs. An independent component analysis (ICA) will be used to remove remaining artefactual components from the EEG signal. Data will be used to compute spectral connectivity in the frontal and parietal areas in the delta, theta and alpha frequencies and expressed in graph theorem-based metrics (e.g., participation coefficient in the alpha band). Further, a set of these graph-theoretic parameters will be extracted from the network analyses and used to train and test a machine-learning model. We will analyze the parameters’ capacity to inform and predict treatment outcome independently (univariate regressions) and combined (multivariate pattern analysis and machine learning).

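### Individual responder status, and through it the four-week stimulation site, is judged on change after active sessions only, so chance change can create responders and site labels without a stimulation effect

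*Protocol article*

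**What the plan says.** The protocol article (Randomized crossover trial) gives each patient two active sessions and two sham sessions, the latter listed as "iii) one sham stimulation over the left DLPFC, and (iv) one sham stimulation over the left AG". On measurement it says: "The CRS-R will be performed before and after each stimulation session". Resting EEG is also recorded before and after every session. A sham change is therefore available for each patient at each site.

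The rules for the individual patient do not use it:

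- **Behavioural responder** (Study objectives and hypotheses): "any patient who displayed new sign(s) of consciousness following stimulation that was never displayed during the screening phase nor at baseline". Primary outcomes repeats this definition and describes the individual-level comparison as post-treatment against pre-treatment.
- **EEG responder** (Secondary outcomes): the alpha-band participation coefficient serves "to determine the response of a patient to the stimulation in the crossover stimulation protocol by means of pre and post stimulation differences".
- **Site for the second phase** (Screening phase & enrollment): the "best behavioral or electrophysiological response to either left DLPFC or left AG stimulation". The Personalized parallel trial section assigns patients "Based on their behavioral (primary) or electrophysiological (secondary) responses to either the left DLPFC or left AG treatment in the crossover RCT" and gives the rule as "DLPFC group if the patient was a responder to the DLPFC stimulation; AG group if the patient was a responder to the AG stimulation". Patients who respond at neither site or at both are randomised 1:1 between sites.
- **Crossover hypothesis** (Study objectives and hypotheses): "a significant portion of our patient sample will show increased responsiveness" after one DLPFC or AG session.

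Sham does appear in the group-level primary comparison (Primary outcomes), in the effect size calculation (Secondary outcomes) and in the expectation about EEG connectivity (Study objectives and hypotheses).

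**The concern.** A new sign after an active session may come from stimulation, from day-to-day fluctuation or from spontaneous recovery. The article gives reason to expect the last two. Its introduction reports an earlier 20 Hz RCT with improvement in all groups, sham being one of them, and patients may enter soon after day 28 post-injury. The same-site sham session is the control that separates these sources, and the individual-level rules leave it out.

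The responder label has several uses. It decides the crossover responder hypothesis and, for patients who respond at one site, the four-week site. It also defines the phenotype aim, the comparison of patients with and without a lesion at the target, and the outcome for the machine-learning classifier. Chance responders dilute each of these. The crossover hypothesis also gives each patient two opportunities to respond and names no sham proportion to compare with, so a positive proportion is expected even when stimulation does nothing.

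**Working it through.** The article states no chance responder rate, so there is no plan figure to reproduce. The planned 90 patients serve only to turn proportions into counts.

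**Inputs.** Two active and two sham sessions per patient (Randomized crossover trial). q is the chance of a new sign in one session with no stimulation effect. It is an assumption, shown over a range. Sessions are taken as independent, also an assumption.

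**Behaviour, no true effect**

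- Responder to at least one active session: 1 − (1 − q)²
- Responder at exactly one site, hence assigned to that site by chance: 2q(1 − q)

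| q | at least one | of 90 | exactly one | of 90 |
|---|---|---|---|---|
| 0.05 | 1 − 0.95² = 9.8% | about 9 | 2 × 0.05 × 0.95 = 9.5% | about 9 |
| 0.10 | 1 − 0.90² = 19.0% | about 17 | 2 × 0.10 × 0.90 = 18.0% | about 16 |
| 0.20 | 1 − 0.80² = 36.0% | about 32 | 2 × 0.20 × 0.80 = 32.0% | about 29 |

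**Behaviour, with a true effect.** Let r be the true response rate per site. The share of observed responders at a site who have no true response is q(1 − r) / [1 − (1 − q)(1 − r)]. With r = 0.20 (assumed):

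- q = 0.05: 0.04/0.24 = 17%
- q = 0.10: 0.08/0.28 = 29%
- q = 0.20: 0.16/0.36 = 44%

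**EEG, no true effect.** If any increase counts, each active session has chance 0.5. Exactly one site: 2 × 0.5 × 0.5 = 50%. Both sites: 25%. Neither: 25%. The last two groups, together 50%, go to the 1:1 step. This applies only to patients whose site behaviour does not settle.

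**What a sham reference achieves.** Suppose a responder must also show no new sign after either sham session. The chance proportion becomes [1 − (1 − q)²](1 − q)²:

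- q = 0.05: 0.0975 × 0.9025 = 8.8%
- q = 0.10: 0.19 × 0.81 = 15.4%
- q = 0.20: 0.36 × 0.64 = 23.0%

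This reduces chance responders but does not remove them. Comparing the active with the sham responder proportion works better: with no effect both have the same expectation (19.0% and 19.0% at q = 0.10), so the expected difference is zero.

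**Subtracting the same-site sham change to pick the site.** Let each session's change have SD s, let the true site difference be s, and let sham effects be equal at both sites. Without subtraction the site contrast has variance 2s², and the better site is picked with probability Φ(1/√2) = 76%. With subtraction the variance is 4s² and the probability is Φ(1/2) = 69%.

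**The case against.** **The sham sessions are used.** Primary outcomes makes sham against active the group-level comparison in both trials, including change in level of consciousness. This stands. A reader might infer that the plan ignores its sham sessions altogether; it does not. The omission concerns individual response, site choice and the responder hypothesis.

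**The behavioural rule has a guard.** The sign must be absent at baseline and at two or more screening CRS-R assessments. This stands and argues for a lower q. It does not cover a sign first seen around a sham session and seen again after a later active one: as worded, only screening and baseline are excluded.

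**EEG is secondary, and its cut-off may be in a fuller document.** Both stand. The EEG proportions do not apply to the whole sample, and the absence of a numeric cut-off from an article is not itself the fault. What the article fixes is the reference, pre against post. A reader might also infer that the 1:1 step would hardly ever be reached, because a continuous difference is almost never zero. The documents do not support this: responders at both sites are randomised too, and in the any-increase model half of patients reach that step.

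**Little harm follows from a site chosen by noise.** Such a patient is in effect randomised to a site, which is the plan's own fallback, and active against sham is randomised 2:1 afterwards. This stands for the validity of the second-phase comparison. It does not rescue the responder proportion, the phenotype or the claim that the site was personalised.

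**A sham correction adds noise.** This stands for site choice by subtraction (76% to 69% above). It does not apply to comparing responder proportions.

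**Conclusion.** The point holds for the individual-level rules. As written, they yield crossover responders and site labels when stimulation has no effect. For q of 5, 10 and 20%, about 10, 19 and 36% of patients respond to at least one active session, and about 10, 18 and 32% to exactly one. These sizes rest on the assumed q and on independent sessions. The EEG figure of 50% at exactly one site rests on the assumption that any increase counts.

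A reader might go further and conclude that chance drives the personalisation, or that the second phase is invalid. The documents support neither. The share due to chance depends on q and on the true effect, and the article gives neither. The 2:1 randomised comparison and the group-level crossover analysis remain valid. What is weakened is the crossover responder hypothesis, the responder phenotype and classifier, and the meaning of a personalised site. The change should be made, and it is cheap.

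**What to change.** 1. Apply the same responder definition to the two sham sessions. Test the crossover responder hypothesis as a within-patient comparison of active and sham responder proportions, by a paired test or a mixed logistic model, and report both proportions side by side.
2. Count a sign as new only if it was absent at every earlier CRS-R, including those around sham sessions.
3. Call an EEG change a response only if it exceeds a limit set from the variability of sham-session changes. All other patients go to the existing 1:1 step. As an illustration, a limit exceeded by chance in 5% of sessions would lower the chance of an increase at exactly one site from 50% to 2 × 0.05 × 0.95 = 9.5%.

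Subtracting each patient's single same-site sham change to choose the site should not be required, because it adds noise to that choice.

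**Cost.** No new visits, recordings or patients. The investigator in charge of randomisation already knows the allocation and can apply the rules without unblinding the assessors. Fewer patients will be labelled responders and more will reach the 1:1 step. Some true responders who also fluctuate will be lost, and some chance responders will remain. Under item 2, a sign gained after one active session can no longer count for the other site in that patient; the randomised session order balances this across the sample.
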